#### Sample size

2.6.3

We did not follow the general method to calculate sample size. The sample size of this study was determined by Ministry of Health and Welfare and Korean Health Industry Development Institute in accordance with study budget, period, and purpose. A total of 100 participants will be recruited, of which 5 will be 20 to 29 years old, 40 will be 30 to 35 years old, 40 will be 35 to 39 years old, and 15 will be 40 to 44 years old. The detail sample size is shown in Table 2, the number of participants by age is based on report of age of the National Supporting Program for Infertile Couples Analysis and Evaluation of supporting project for infertile couples in 2012.^[21]^ Age distribution of participants supported by IVF is shown in Table 3.

**Table 2 T2:**
[figure not shown]
Sample size according to age group.

**Table 3 T3:**
[figure not shown]
Age distribution of participants supported by IVF.

### Study visit and data collection

2.7

#### In case of pregnancy failure

2.7.1

The clinical study flow chart in case of pregnancy failure is shown in Table 4.

**Table 4 T4:**
[figure not shown]
Study flow chart in case of pregnancy failure.

#### In case of pregnancy success

2.7.2

The clinical study flow chart in case of pregnancy success is shown in Table 5.

**Table 5 T5:**
[figure not shown]
Study flow chart in case of pregnancy success.

### Statistical analysis

2.8

The analysis set will comprise a full analysis set and a per-protocol set. Descriptive analyses including the mean, standard deviation, and frequency will be undertaken describing the baseline characteristics of participants. Continuous variables of primary and secondary outcomes will be presented in descriptive statistics and categorical data will be presented in frequency and percentage. When comparing and analyzing according to the level of specific variables such as demographic variables, continuous data will be tested using a Student's *t*-test or Wilcoxon's rank sum test. Categorical data will be analyzed using a chi-squared test or Fisher's exact test. For before and after comparisons, a paired *t*-test or Wilcoxon's signed rank test will be used. Repeated measures ANOVA will also be performed, whereas McNemar's test will be performed on categorical data. All statistical analyses will be conducted at a significance level of 0.05 and tested on both sides. Statistical analysis will be performed using the SAS program (version 9.4; SAS Institute Inc., Cary, NC).

#### Missing data

2.8.1

Upon analysis of the validation variables, if the data are missing at some point or the subject is missing, the last observation carried forward (LOCF) analysis will be performed as if it were obtained at that time. The LOCF analysis applies to all validation analyses.

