#### Primary outcome

2.6.1

The primary outcome of this study will be CPR. Clinical pregnancy was considered to be at least 1 gestational sac with fetal heart activity confirmed by ultrasound scan 5 to 6 weeks after pregnancy.^[18]^

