#### Secondary outcome

2.6.2

The secondary outcome of this study will be implantation rate (IR), ongoing pregnancy rate (OPR), and live birth rate. IR is confirmed by at least 1 gestational sac after human chorionic gonadotropin positive.^[19]^ Ongoing pregnancies are defined as the presence of fetal cardiac activity beyond 12 weeks of gestation.^[20]^ OPR is defined as the number of ongoing pregnancies divided by the number of clinical pregnancies. Live birth is defined as the delivery of 1 or more living infant (have heart beats or have beats of umbilical cord or have definite movement of voluntary muscles).

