### Trial status

3.1

Patient recruitment is ongoing. Patient enrollment and trial completion is expected by May of 2018.

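### LOCF is prescribed for every efficacy analysis, but the outcomes are one-off pregnancy milestones: it inflates the ongoing pregnancy rate, is undefined for live birth, and for clinical pregnancy is conservative

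*Protocol article*

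**What the plan says.** Section 2.8.1 (Missing data) gives one rule, triggered by a missing time point or a missing subject: "the last observation carried forward (LOCF) analysis will be performed as if it were obtained at that time". The carried value is thus treated as if it had been observed at the missing time. The scope is total: "The LOCF analysis applies to all validation analyses". Beside the outcome sections, *validation* can only sensibly mean efficacy. No exception, alternative or sensitivity analysis is stated.

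The outcomes that the rule must serve are in 2.6.1 and 2.6.2:

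- Clinical pregnancy (primary, CPR): "at least 1 gestational sac with fetal heart activity confirmed by ultrasound scan 5 to 6 weeks after pregnancy".
- Ongoing pregnancy: "Ongoing pregnancies are defined as the presence of fetal cardiac activity beyond 12 weeks of gestation". Its rate has its own denominator: "OPR is defined as the number of ongoing pregnancies divided by the number of clinical pregnancies".
- Live birth: "Live birth is defined as the delivery of 1 or more living infant".

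Section 2.2 gives 4 treatment cycles and 3 observation cycles. Section 2.10 lets only women with at least 70% compliance continue, so some early leaving is built into the design.

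**The concern.** LOCF presumes a state that is measured repeatedly and stays roughly constant after the last visit. Pregnancy milestones are not like that. The 12-week outcome is recorded because some pregnancies with an early heartbeat do not reach it, and LOCF assumes that question away for each woman who lacks the later scan.

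The trial has a single arm, so no control group shares the error. The Discussion says that literature on assisted reproduction will replace the control group, for effectiveness and for cost-effectiveness, and that the results will inform national policy. A rate shifted by the missing-data rule goes straight into that comparison.

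**Working it through.** The article states no dropout rate, pregnancy-loss rate or expected number of pregnancies, so there is no figure of its own to reproduce. All rates below are assumptions, apart from 10% and 33.5%, which the Background cites for IUI and IVF and which serve here only as a range for the true CPR.

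**1. Ongoing pregnancy.** Let l be the fraction of clinical pregnancies without the later scan and m the true loss rate between the two scans, the same in women with and without it. Every lost woman is in the denominator already, and LOCF puts her in the numerator:

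LOCF OPR = (1 − l)(1 − m) + l, so bias = l × m.

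- m = 0.20, l = 0.20: 0.80 × 0.80 + 0.20 = 0.84, against a true 0.80.
- m = 0.20, l = 0.40: 0.60 × 0.80 + 0.40 = 0.88.

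Upward bias in percentage points:

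| l | m = 10% | m = 20% | m = 30% |
|---|---|---|---|
| 1/15 | 0.7 | 1.3 | 2.0 |
| 20% | 2.0 | 4.0 | 6.0 |
| 40% | 4.0 | 8.0 | 12.0 |

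In counts, suppose 15 clinical pregnancies, m = 20% and L women lost:

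| L | LOCF: ((15 − L) × 0.8 + L)/15 | Unknown = not achieved: (15 − L) × 0.8/15 |
|---|---|---|
| 1 | 81.3% | 74.7% |
| 2 | 82.7% | 69.3% |
| 3 | 84.0% | 64.0% |

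With 3 women lost, the two scorings differ by 3/15 = 20 points. Among the 12 women with known outcome the estimate is 9.6/12 = 80%, which is right provided that the lost women resemble the rest.

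**2. Live birth.** Delivery cannot be observed at an earlier visit, so the rule must borrow either the state pregnant or the state not delivered. With 15 clinical pregnancies, 80% of them ending in a birth and 3 women lost, the truth is 15 × 0.8 = 12 births.

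- Pregnant carried to birth: 12 × 0.8 + 3 = 12.6 births.
- Not delivered carried forward: 12 × 0.8 = 9.6 births.

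The article does not say which state is carried, so even the sign of the bias is open.

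**3. Clinical pregnancy.** A woman who leaves without a pregnancy is carried forward as not pregnant. Assume a constant chance q per cycle over 7 cycles, with 1 − (1 − q)^7 = true CPR, and unrelated dropout h at the end of each cycle, with 1 − (1 − h)^7 = total dropout. With r = (1 − q)(1 − h):

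LOCF CPR = q(1 − r^7)/(1 − r).

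| True CPR | 10% dropout | 30% dropout |
|---|---|---|
| 10% | 9.6% | 8.7% |
| 20% | 19.2% | 17.4% |
| 33.5% | 32.1% | 29.2% |

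Earlier leaving costs more. With 3% per cycle and 30% of women all leaving after cycle 2, LOCF gives 0.7 × (1 − 0.97^7) + 0.3 × (1 − 0.97^2) = 15.2%, against a true 1 − 0.97^7 = 19.2%. For scale, the standard error of a 20% rate with 100 women is √(0.2 × 0.8/100) = 4 points.

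**The case against.** The strongest defence is that the harm is small where it matters most. For the primary outcome, missing = not pregnant cannot inflate a single-arm rate, and with dropout spread evenly over the cycles the understatement stays within one standard error at a true rate of 20%. A life-table with censoring is not plainly better: it assumes that leaving is unrelated to the chance of conceiving, whereas 2.10 removes women for low compliance. All of this stands, and it limits the CPR part to making the rule explicit and adding a sensitivity analysis.

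Second, the obvious replacement, scoring every unknown as not achieved, can be further from the truth than LOCF. Under the 80% and 20% assumptions it gives 64%, an error of 16 points against 4. This also stands: that scoring belongs in a bound and should not be the main estimate.

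Third, LOCF might be said to carry only each variable's own last value, so that a lost pregnancy would count as a failure. For live birth that reading is possible, which is why no direction is claimed. It is less natural for ongoing pregnancy, which is defined by the same sign as clinical pregnancy, seen later.

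Three stronger conclusions are tempting but unsupported:

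- *Live birth is overstated.* This holds only if the state carried is pregnancy.
- *Pregnancies still in progress at trial close will be scored as births.* Section 3.1 says only that "Patient enrollment and trial completion is expected by May of 2018". Follow-up after conception is in Table 5, which is not shown and may run to delivery.
- *The stated precision is wrong.* The article states no standard error or confidence interval for any of these rates.

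**Conclusion.** The rule as written does not suit the outcomes it governs. This is an explicit commitment and not a detail left to a fuller document. It should be fixed, but it does not undermine the primary result.

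- **OPR:** biased upward whenever a woman is lost after the early scan and later loss is possible. The size is l × m: 4 points (84% against 80%) at 20% lost and 20% later loss, and 0.7 to 12 points over the range shown. This rests on the literal carry-forward of fetal heart activity and on equal loss rates in women with and without the later scan.
- **Live birth:** no valid value to carry, and the direction of error is undetermined.
- **CPR:** conservative. The understatement is modest at low dropout and larger if many women leave early. A reader might infer serious damage to the primary outcome, but the article gives no dropout rate that would support this.

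**What to change.** Rewrite 2.8.1 for the pregnancy outcomes:

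1. Remove LOCF for these outcomes and state that an earlier milestone never stands in for a later one.
2. Report OPR and live birth among women with known outcome, always with a worst-case bound (unknown = not achieved), a best-case bound (unknown = achieved) and the number unknown.
3. For CPR, keep missing = not pregnant and name it as the conservative analysis. As a sensitivity analysis, add a life-table estimate by cycle, censored at the last observed cycle. State that it assumes non-informative dropout, and that the compliance rule in 2.10 puts this assumption in doubt.

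The cost is one rewritten paragraph and a little more programming, with no extra participants. The drawback is that the bounds will be wide if several pregnancies have unknown outcome: 3 unknown among 15 gives a span of 20 points, from 64% to 84% in the example above. That width shows how much the data leave open, which LOCF would hide.

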### Additional analysis

2.9

#### Safety evaluation

2.9.1

At each visit, any subjective and objective discomforts will be collected through interviews, after which these will be recorded on patients case report form (CRF). The clinical laboratory tests will be performed before and after the treatment period to check for hematologic problems.

#### Economic evaluation

2.9.2

Economic evaluation will be conducted from a social perspective and all costs and results will be considered. The cost data per patient in this trial will be requested to submit medical institutions or card receipts for expenses incurred in the preclinical treatment. If patients cannot submit a receipt, we will conduct a survey of preclinical treatment cost. The cost of this trial will be calculated by converting this trial treatment schedule into a general treatment. Transportation costs and time costs will be used to existing values that patients had spent, and surveys will be conducted during the clinical trial period.

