### Design/setting

2.2

This study was designed as a multicenter, single-arm prospective clinical trial. All participants included will be from 3 hospitals: Dongguk University Ilsan Korean Medicine Hospital, Kangdong Kyunghee Korean Medicine Hospital, and Wonkwang University Kwangju Korean Medicine Hospital. Participants will be recruited through advertisements on bulletin boards at each medical center. The total target sample size is 100 subjects. All participants will voluntarily sign an informed consent agreement. Moreover, all participants will be enrolled after screening via the inclusion/exclusion criteria. All recruited patients will perform related surveys and tests, and be provided with treatments (herbal medicine, acupuncture, moxibustion). They will undergo an approximately 4 menstrual cycle treatment period and a 3 menstrual cycle observation period. If pregnancy occurs during the study, we will offer the herbal medicine to participants for about 15 days. The costs spent (transportation, time, care) in the previous treatment of the participants of this clinical trial will be investigated and compared with the conversion cost of this trial.

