#### Acupuncture and moxibustion

2.5.2

All patients will receive acupuncture treatment on 14 acupoints, GV20, CV4, bilateral Ex-CA7, ST29, SP6, SP9, ST36, and PC6 using acupuncture needles 0.3 mm in diameter and 30 mm in length (Dong Bang, Gyeonggi-do, Korea). At GV20, practitioners will insert needles 5 mm into the scalp fascia. At other acupoints, needle insertion will be to a depth of 15 to 20 mm, depending on the region of the body into which the needles were inserted. These procedures will elicit de-qi sensation. We will use electro-acupuncture for maintain de-qi and infrared therapy to heat the lower abdomen. The electro stimulation will be administered for 20 minutes at low-continuous 2 Hz. Following elicitation of the de-qi sensation at CV4, we will apply moxibustion for 20 minutes. Acupuncture and moxibustion treatments will be performed at MCD 3, 8, and 14 during 4 menstruation cycles. If the patient becomes pregnant during treatment, these treatments will be stopped.

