### Quality assurance

2.10

We will set qualification standards to make sure that patients are treated in according with this trial. Therefore, we will inform all practitioners of the details of this trial. Treatment will be performed by doctors of Korean medicine who have extensive clinical experience with acupuncture and moxibustion. Specifically, they will be graduates of a 6-year full-time course in Korean Medicine, taught as a college program, certified by the Korean Ministry of Health and Welfare as a Korean Medicine Doctor, and have more than 1 year of postgraduate clinical training in a Korean Medicine hospital. Compliance of herbal medicine, acupuncture, and moxibustion should be in the range of 80% to 120% per visit. In this trial, only subjects with compliance of 70% or more will continue the study.

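### The economic evaluation costs Korean medicine from the trial schedule, although treatment received varies with pregnancy and compliance; delivered quantities should be priced instead

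*Protocol article*

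**What the plan says.** Section 2.9.2 (Economic evaluation) sets a broad scope: "Economic evaluation will be conducted from a social perspective and all costs and results will be considered". For KM treatment itself it gives one rule: "The cost of this trial will be calculated by converting this trial treatment schedule into a general treatment". The other cost sources in that section concern different items. Receipts, or a survey where receipts are lacking, cover care before the trial. For travel and time the text reads: "Transportation costs and time costs will be used to existing values that patients had spent, and surveys will be conducted during the clinical trial period". Section 2.2 (Design/setting) says that participants' earlier treatment costs "will be investigated and compared with the conversion cost of this trial".

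Three other places make the quantity of treatment depend on what happens to the woman:

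- Section 2.5.2 (Acupuncture and moxibustion) sets the plan, "Acupuncture and moxibustion treatments will be performed at MCD 3, 8, and 14 during 4 menstruation cycles", and then the exception: "If the patient becomes pregnant during treatment, these treatments will be stopped".
- Section 2.2 adds treatment after conception: "If pregnancy occurs during the study, we will offer the herbal medicine to participants for about 15 days".
- Section 2.10 (Quality assurance) ends participation for poor adherence: "In this trial, only subjects with compliance of 70% or more will continue the study".

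**The concern.** The object being converted to a cost is a schedule, not a record of care. The schedule that the article describes is four cycles of two prescriptions with three acupuncture and moxibustion sessions per cycle. A woman who conceives in cycle 1 has far fewer sessions than that. A woman who conceives in cycle 4 or later has the full schedule plus the course offered after pregnancy. A woman who falls below the compliance limit leaves with part of it unused.

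Costing everyone at the schedule has two consequences. First, KM treatment cost becomes a constant, so it cannot covary with pregnancy and adds nothing to the uncertainty around cost-effectiveness. Travel and time costs may still vary, because they are surveyed. Second, the mean treatment cost may be off. There is also an asymmetry: earlier care is costed woman by woman from receipts or a survey, while KM is costed from a template. Cost-effectiveness relative to assisted reproduction is a stated aim (section 2.1), and the Discussion says that the results are to support national policy.

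**Working it through.** The article gives no cost, unit price or cost-effectiveness ratio, so there is no figure to reproduce. The check counts treatment units.

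**Inputs from the article**
- Sessions: 3 per cycle × 4 cycles = 12 (section 2.5.2).
- Herbal packs: 30 of each of two prescriptions (section 2.5.1).
- Four treatment cycles and three observation cycles (section 2.2).
- Pregnancy rates of 10% (insemination) and 33.5% (in vitro fertilisation) from the Background. They are borrowed only as an illustrative range for the proportion pregnant over seven cycles; the article states no expected rate for KM.

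**Assumptions**
- The 30 + 30 packs are supplied per cycle, so the plan is 60 × 4 = 240 packs.
- The course after pregnancy is taken twice daily: 15 × 2 = 30 packs.
- A woman who conceives in cycle k has all of that cycle's treatment.
- The regular herbal courses are not continued after conception. The article ties them to menstrual cycle days but does not state this.
- No one leaves for other reasons.

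**Per woman.** Conception in cycle k gives 3·min(k,4) sessions and 60·min(k,4) + 30 packs.

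| Cycle of conception | Sessions (plan 12) | Packs (plan 240) | Packs minus plan |
|---|---|---|---|
| 1 | 3 | 90 | −150 |
| 2 | 6 | 150 | −90 |
| 3 | 9 | 210 | −30 |
| 4 | 12 | 270 | +30 |
| 5 to 7 | 12 | 270 | +30 |

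Among women who conceive, sessions vary fourfold (3 to 12) and packs threefold (90 to 270). A fixed-schedule cost shows none of this.

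**Cohort mean, constant hazard.** Let P be the proportion pregnant over seven cycles and q = (1 − P)^(1/7). Mean treated cycles are S = 1 + q + q² + q³. Mean sessions are 3S and mean packs are 60S + 30P.

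- P = 0.10: q = 0.9851, S = 3.911. Sessions 3 × 3.911 = 11.73; 12/11.73 = 1.023. Packs 234.7 + 3.0 = 237.7; 240/237.7 = 1.010.
- P = 0.335: q = 0.9434, S = 3.673. Sessions 3 × 3.673 = 11.02; 12/11.02 = 1.089. Packs 220.4 + 10.05 = 230.4; 240/230.4 = 1.042.

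| P | Mean sessions | Plan too high by | Mean packs | Plan too high by |
|---|---|---|---|---|
| 10% | 11.73 | 2.3% | 237.7 | 1.0% |
| 15% | 11.59 | 3.5% | 236.4 | 1.5% |
| 20% | 11.45 | 4.8% | 234.9 | 2.2% |
| 33.5% | 11.02 | 8.9% | 230.4 | 4.2% |

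Whatever the unit prices, the error in the combined cost of sessions and packs lies between the two percentages in a row.

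**Sensitivity to timing.** At P = 33.5%, if every conception fell in cycle 1, the plan would be too high by 33.6% (sessions) and 26.5% (packs). If every conception fell in the observation cycles, sessions would be exact and packs too low: 240/(240 + 30 × 0.335) = 240/250.05 = 0.960, or 4.0% under. At P = 10% the latter is 240/243 = 0.988, or 1.2% under. The same two pack figures apply if the regular herbal courses were continued after conception.

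**Sensitivity to the pack count.** Counting doses by day (10 + 16 days, twice daily) gives 52 per cycle and 208 in all. The plan is then too high by 208/(52 × 3.911 + 3.0) = 1.008 at P = 10% and 208/(52 × 3.673 + 10.05) = 1.035 at P = 33.5%. The pattern is the same.

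**The case against.** The sentence does not say planned, fixed or four-cycle. It can be read as repricing trial care at routine prices, which concerns price and leaves quantity open. The study schedule also has two branches, with separate flow charts for pregnancy failure and success (Tables 4 and 5, whose contents are not available here). The success branch may already hold the stop and the added course. The article condenses a fuller protocol, where counting rules may sit. The evaluation is listed under additional analysis, the likely error is a few percent, and where it overstates KM cost it works against KM.

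Much of this stands, and it rules out stronger readings:

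- A reader might infer that every woman will certainly be charged four cycles, or that the course after pregnancy is certainly left out. Neither is stated.
- A reader might infer that KM cost is overstated more and more as KM works better. The documents do not support this. Early conception saves treatment and the added course costs more, so the sign depends on when conceptions occur.
- A reader might take it as given that the regular prescriptions end at pregnancy. Section 2.5.2 stops only acupuncture and moxibustion.
- Early leaving for low compliance would also separate schedule from care. The article gives no rate, so no percentage can be attached to it.

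The objection does not remove the point. This is a rule that the article states, not a detail it omits, and on its natural reading the schedule is the unit costed. Even a two-branch schedule cannot give a woman's cost without her cycle of conception and what was delivered. If the sentence means repricing only, it still does not say which quantities are repriced.

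**Conclusion.** The point holds as a moderate one: the stated costing rule should be changed, but it is not shown to produce a wrong result. Pricing delivered care is better than the stated method. The main loss, if the fixed schedule is priced, is that KM treatment cost no longer varies between women or with pregnancy. That loss remains even where errors in the mean cancel. The mean error is secondary: about 1% to 9% too high at 10% to 33.5% pregnant under a constant hazard, with herbal use 30 packs too low for each conception in cycle 4 or later. These sizes rest on the borrowed pregnancy range, the assumed pack supply and twice-daily added course, the assumption that regular herbal courses are not continued after conception, and no other early stopping. The primary outcome is not affected.

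**What to change.** Replace the costing sentence in section 2.9.2 with wording such as: *Each woman's KM treatment cost is the number of herbal packs and acupuncture/moxibustion sessions actually delivered to her, including any herbal course given after pregnancy, each multiplied by its general-practice unit price. The cost of the full four-cycle schedule is reported as a sensitivity analysis.*

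This changes no treatment rule and adds no visits or participants. The compliance check in section 2.10 already needs counts of treatment taken, so the cost is the wording plus a small amount of analysis work to sum quantities per woman.
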